### 2.10. Clinical Outcome Definitions and Clinical Assessment Methods

#### 2.10.1. Infant Medically Diagnosed Eczema

Infant medically diagnosed eczema is defined by typical eczema skin lesions [42] clinically observed by a medical practitioner. The extent and severity of any active eczema at the in-person infant review appointments will be scored according to the standardized SCORAD severity index [43].

#### 2.10.2. Infant Medically Diagnosed Recurrent Wheeze

Infant medically diagnosed recurrent wheeze is defined as more than one separate episode of wheeze symptoms clinically observed by a medical practitioner.

#### 2.10.3. Infant Allergen Sensitisation

Infant allergen sensitisation is defined as a positive skin prick test (with mean weal diameter ≥ 3 mm above the control weal size) to at least one food and/or environmental allergen at 1 year of age. The participating infants are skin prick tested to egg, cow’s milk, wheat, fish (tuna), peanut, cashew nut, ryegrass pollen, cat and house dust mite (Dermatophagoides pteronyssinus), with histamine and control solutions, using commercial extracts, and in accordance with standard clinical methods.

#### 2.10.4. Infant IgE-Mediated Food Allergy

Infant IgE-mediated food allergy is defined as a history of immediate IgE-mediated symptoms (within 60 min of food ingestion) including angioedema, urticaria, cough, wheeze, stridor, vomiting, diarrhoea and/or cardiovascular symptoms; and specific food allergen sensitisation to the same food detected by a positive skin prick test (as described above).

#### 2.10.5. Skin Barrier Permeability

Maternal and infant skin barrier permeability is assessed by measuring trans epidermal water loss (TEWL), a measure of which determines to the skin’s ability to retain moisture, measurements are conducted using the Biox Aquaflux AF200 (Biox Systems Ltd., London, UK).

#### 2.10.6. Body Composition

Infant birth body composition is assessed by using the through air-displacement plethysmography PEA POD body composition system (Cosmed, Rome, Italy) up to 96 h after birth to measure infant fat mass, fat-free mass, percentage body fat and percentage fat-free mass.

### 2.11. Laboratory Outcomes Assessment Methods

Biological samples (blood, stool and breast milk) analyses will be done on pre-determined subsets of the participants to determine the effects of the intervention. The use of longitudinal biological sample collections, and assessing changes from the 20 weeks’ gestation baseline, will reduce potential influences of inter-women variations in chronic health status, diet, lifestyle and environment. The results of these laboratory outcome assessments are planned to be published separately to the primary outcome clinical findings paper. 

#### 2.11.1. Blood Samples

Blood samples (maternal, cord blood and infant) are being analysed for innate and adaptive immune responses. These include maternal serum inflammatory biomarkers (especially IL-1β, IL-6 and TNF-α); cord blood and infant cytokines responses, including IL-6, TNFα, IL-1β, IL-12 and IL-10); effector T cell responses to mitogens and allergens, and Th2 (IL-13, IL-5), Th1 (IFNγ) and IL-10 responses in the supernatants; and regulatory T cell responses, including the numbers and function of CD4(+)C25(+)CD127(low/−) cells, and expression of regulatory marker FOXP3+. 

#### 2.11.2. Stool Samples

Stool samples (both maternal and infant) are being analysed for gut microflora colonisation patterns and stool short-chain fatty acid profiles. Our prime approach is based on extraction of DNA, amplification using 16S primers, and sequencing using the Illumina MiSeq platform. We are assessing qualitative and quantitative information on bacterial species, microbial diversity and ordination. Individual stool sample (both maternal and infant) short chain fatty acid (SCFA) concentrations of acetic, propionic, butyric, isobutyric, valeric, and isovaleric acid are also being analysed, along with determining the relative proportions of the sum of all acids quantified.

#### 2.11.3. Breast Milk Samples

Breast milk samples are being analysed for the measurement of immunoglobulins (including secretory IgA, allergen-specific IgA and IgG4); cytokines/chemokines (including IL-1beta, IL-4, IL-5, IL-6, IL-10, IL-13, IL-27, IL-33, and TNF alpha); growth factors (including epidermal growth factor and insulin like growth factor-I); human milk microbiome; human milk oligosaccharide profiles; and macro- and micro-nutrient composition. 

### 2.12. Study Timeline

Figure 1 summarises the participants schedule of appointments and biological sample collections. Before 21 weeks’ gestation, informed consent including a screening form checklist is completed. At 18–20 weeks’ gestation baseline data are recorded, including basic demographic information; maternal, paternal and any sibling history of allergic disease; maternal and paternal ethnicity and education; and any prior prebiotics or probiotics supplements use. Maternal weight and height are measured, and pre-pregnancy weight recorded. Baseline blood and stool samples are collected. 

Each month during the intervention period, from 18–20 weeks’ gestation until 6 months’ post-partum, the participating women are asked about their compliance with the study powder ingestion, any adverse gastrointestinal symptoms, stool frequency and consistency, any use of other prebiotics, probiotics or antibiotics, and any hospitalisations for >24 h duration. Maternal in-person appointments in pregnancy also occur at 28 and 36 weeks’ gestation, when weight and TEWL (36 weeks only) are measured, and blood and stool samples are collected.

After birth, data on infant sex, birth weight, length, head circumference, and mode of delivery details are collected. Infants also have a body composition measurement up to 96 h after birth. A sample of cord blood is collected where possible at delivery. 

Postnatal telephone calls occur at 1, 2 and 5 months of age. Data are also collected to prospectively capture information on infant feeding and to document any infant allergy symptoms. At the 1 month phone call, participants are reminded to collect a breast milk sample, as well as a maternal and infant stool sample when the infant is 2 months of age. These are frozen in the home freezer until they are brought in at the 3–4 month visit.

Postnatal appointments occur at 3–4 and 6 months of age, when maternal weight and TEWL is measured, and infant TEWL and anthropometric measurements (length, weight, head circumference) are taken. Data collection also includes infant feeding (including solid foods introduction), use of any probiotics or antibiotics, hospitalisations for >24 h duration, and history of wheeze and/or eczema symptoms. The infant is examined for clinical signs of allergic disease (ie eczema), and SCORAD [43] (severity and extent of eczema) assessments performed if relevant. At these visits the following samples are also collected: infant blood, maternal blood (3–4 months only), infant and maternal stool and breast milk. 

At 1 year of age (between 12–18 months of age), a child follow-up appointment will collect data on infant feeding (including solid foods introduction), use of antibiotics, hospitalisations (>24 h duration), history of wheeze and/or eczema symptoms, examination for clinical signs of allergic disease (i.e., eczema), and SCORAD (severity and extent of eczema) if relevant. Child TEWL and anthropometric (length, weight, head circumference) measurements are taken. Child blood, stool and breast milk samples are collected. The child also has allergy skin prick testing to determine allergen sensitisation status as described above.

### 2.13. Serious Adverse Event Monitoring

A blinded independent Serious Adverse Event (SAE) Committee consists of an obstetrician, an allergist/immunologist and a neonatologist/paediatrician. This committee meets as required to review any deaths, admissions to intensive care hospital care or other serious adverse reactions. The primary role of the SAE Committee is to review all SAEs to determine whether there is any likelihood that involvement in the trial could have contributed to the event. The cause of the event is determined from the autopsy results or other hospital summary of the event by the relevant medical personnel. In case of any potential safety concerns observed by the SAE Committee, these are communicated to the trial Chief Investigators ([name] and [name]) who also inform the governing Ethics Committee.

### 2.14. Data Collection and Management

Trial monitoring to ensure compliance with good clinical practice and the study protocol is conducted by a Chief Investigator ([name]) every six months, or as required, to ensure the integrity of the trial. Data are collected by trained research personnel and entered directly into an electronic case-report form with password protection and defined user-level access. Research Electronic Data Capture (REDCap) is used to facilitate trial management and data collection. A record of all women successfully screened for eligibility and consented is recorded in real time. Once consented and randomised, REDCap automatically calculates study milestones for each participant. This information is readily available for research staff to enable scheduling of appointments and phone calls. The electronic case report form has inbuilt data entry validity checks to ensure immediate resolution of data queries. Summary reports including screening data, enrolment, withdrawals, appointment attendance and study completion are generated from REDCap for regular Chief Investigator review of trial progress. Electronic data are stored on secure servers at the Telethon Kids Institute with access only granted to authorised study personnel and released only to persons authorised to receive those data. All data collected is treated with confidence.

### 2.15. Sample Size

Based on infant medically diagnosed eczema by 12 months of age as the primary outcome, with an expected background rate of 30% in this ‘at risk’ population due to family history of allergic disease [44,45], 293 participants per group will be required to achieve a relative reduction of 33% (to a rate of 20%) in the intervention group (two-tailed alpha = 0.05, 80% power). Maternal probiotics supplementation [46]) has been shown to significantly reduce infant eczema in a smaller ‘at risk’ population. Allowing for a 10% dropout, a total sample size of 652 (326 per group) allows for an adequate sample size for this trial.

### 2.16. Statistical Analysis

Analyses will be performed on an intention-to-treat basis (i.e., all randomised women analysed as randomised). For the primary outcome, the proportion of infants with medically diagnosed eczema by 12 months of age will be compared between groups using log binomial regression. Adjustment will be made for variables used to stratify the randomisation, with the difference between groups expressed as an adjusted relative risk with a confidence interval and two-sided *p*-value. Differences in secondary clinical outcomes will be examined in the same way. A sensitivity per-protocol analysis of the primary outcome will be undertaken in women that consumed at least 75% of their allocated study powder (based on return weights) during the entire intervention period (<21 weeks gestation to 6 months post-natal). Another sensitivity per-protocol analysis of the primary outcome will be undertaken in women that consumed their allocated study powder on at least 75% of the days between randomisation and 36 weeks of gestation (last clinic visit prior to birth).

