## 1. Introduction

Allergic diseases are now among the most common chronic diseases of childhood, with eczema/atopic dermatitis now affecting up to one-in-five infants and food allergy in one in ten infants in affluent societies [1]. Eczema/atopic dermatitis and food allergies commencing during infancy are the earliest manifestations of allergy, and reflect the vulnerability of the immune system to modern diet, lifestyle and environmental changes. Diet is a major determinant of gut microbiota composition and function [2,3], which in turn can be associated with inflammation and immune dysfunction [4]. Hence, the role of dietary composition in increasing commensal microbial gut diversity has emerged as one of the critical factors for beneficial immune health. 

Prebiotics are defined as substrates that are selectively utilized by host microorganisms conferring a health benefit [5]. Prebiotics are recognized as key immune-modulating nutrients, which selectively stimulate growth of beneficial gut microbiota—with prebiotic fermentation products, such as short-chain fatty acids (SCFA), that have direct local gut and systemic anti-inflammatory effects [5]. Microbial-derived SCFA are recognised as essential mediators in the communication between the intestinal microbiome mucus barrier and the immune system, and are considered as a likely pathway by which the gut microbiota influences immune health [6]. SCFA influence host immune responses through several key pathways [7] including: (1) promoting intestinal barrier integrity; (2) binding to ‘metabolite-sensing’ G-protein-coupled receptors such as GPR43, GPR41, and GPR109A, which promote gut homeostasis and the regulation of inflammatory responses [8,9,10]; and (3) inhibition of Histone Deacetylases which regulate rapamycin (mTOR)-S6K pathways required for T cell differentiation into effector and regulatory cells [11,12]. Along with the mTOR pathways, SCFA also enhance the activation of STAT3 (Signal transducer and activator of transcription 3), which is involved in the expression of cytokines (IL-10, IL-17, and IFN-γ) in T cells [12]. Collectively, these have the potential to alter the differential balance of Th1 versus Th2 immune differentiation, and as a consequence reduce the risk of allergic responses [11,12].

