### 2.2. Participant Eligibility

The inclusion criteria for this study are: (1) pregnant women < 21 weeks of gestation, whose infants have a first-degree relative (mother, father or sibling) with a history of medically diagnosed allergic disease (asthma, allergic rhinitis, eczema and/or food allergy); and (2) ability to provide informed consent. The gestational age is calculated from first trimester ultrasounds, or, if not available, the date of the last menstrual period. The exclusion criteria for this study are: (1) maternal smoking during pregnancy [40]; (2) maternal age < 18 years; (3) women already consuming prebiotic supplements (>twice per week); and (4) women who have a diagnosed cow’s milk allergy or lactose intolerance.

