### 2.4. Randomisation and Allocation to Treatment Groups

Once written consent has been obtained, each participant is randomised to one of two groups and assigned a unique uninformative five-digit study identification number (Study ID) according to a randomisation schedule via a secure web-based randomisation process. The Study ID number also corresponds to a matching Study ID labelled box of study powder tins to be provided to that participant. The computer-generated randomisation schedule is stratified, using randomly permuted, size-balanced blocks, by maternal allergy status (history of medically diagnosed asthma, allergic rhinitis, eczema and/or food allergy) and maternal pre-pregnancy body mass index (BMI < 25 or ≥25). The randomisation schedule is prepared by an independent statistician not involved with trial participants or data analysis. Randomisation codes are maintained by researchers working independently of the trial. Investigators and participants will not be unblinded until all the participating infants have completed their 12 month of age outcome assessments.

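### Paternal and sibling allergy history are collected at baseline but not named as covariates in the primary model; prespecifying them could give a modest gain in precision

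*Protocol article*

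**What the plan says.** Protocol article, section 2.16: the proportion of infants with medically diagnosed eczema by 12 months "will be compared between groups using log binomial regression". On covariates it says "Adjustment will be made for variables used to stratify the randomisation", and the result is an adjusted relative risk.

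Section 2.4 names two stratification variables: maternal history of allergic disease, and maternal pre-pregnancy BMI below 25 versus 25 or above.

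Section 2.2 admits women "whose infants have a first-degree relative (mother, father or sibling) with a history of medically diagnosed allergic disease". Mother, father and sibling therefore count equally for entry.

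Section 2.12 lists "maternal, paternal and any sibling history of allergic disease" among the data recorded at 18–20 weeks' gestation.

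Section 2.15 assumes a 30% background rate in this population "due to family history of allergic disease". Section 1 describes "eczema/atopic dermatitis now affecting up to one-in-five infants" in affluent societies.

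**The concern.** Of the three kinds of family history that define the trial population, only the mother's is named for the primary model. Maternal status does separate one group: an infant without maternal history must have qualified through the father or a sibling. It does not distinguish father from sibling, or one affected relative from several.

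The investigators thought maternal history important enough to stratify on, and they attribute the raised background rate to family history. That makes the father's and siblings' histories natural candidate covariates. Randomisation does not balance them by design. If they predict eczema, leaving them out gives a somewhat wider interval for the relative risk and no correction for chance imbalance. What is at stake is precision. Section 2.17 reports recruitment complete at 652, so adjustment is one of the few ways left to gain any.

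**Working it through.** **1. The plan's own figure.** Inputs from section 2.15: 30% versus 20%, two-sided alpha 0.05, 80% power, 10% dropout. With pooled variance:

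n = [1.960 × √(2 × 0.25 × 0.75) + 0.842 × √(0.30 × 0.70 + 0.20 × 0.80)]² / 0.10² ≈ 293.2

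This is 294 per group if rounded up, and power at 293 is 80.0%. Then 293 / 0.90 = 325.6, so 326 per group and 652 in total. The stated figures reproduce. They rest on an unadjusted comparison and do not rely on covariates.

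**2. Starting point on the log relative risk scale, 293 per group.**

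SE = √[0.70/(0.30 × 293) + 0.80/(0.20 × 293)] = 0.1470

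Power = Φ(0.4055/0.1470 − 1.960) = 78.8%, where 0.4055 = |ln(0.20/0.30)|.

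**3. Assumed eligible population.** The documents give neither prevalence nor prognostic strength for the relatives' histories. Assumed before the eligibility rule: mother affected 60%, father 50%, half of infants with a sibling, and 35% of those siblings affected (0.5 × 0.35 = 17.5% overall). Families with no affected relative (0.40 × 0.50 × 0.825 = 16.5%) are removed, because section 2.2 excludes them. The lowest risk level is set so that the control group averages 30%. For relative risk 1.5 for each relative, the mean multiplier is [(0.4 + 0.6 × 1.5)(0.5 + 0.5 × 1.5)(0.825 + 0.175 × 1.5) − 0.165] / 0.835 = 1.919. The base risk is then 0.30/1.919 = 0.156, and the highest-risk control cell is 0.156 × 1.5³ ≈ 0.53.

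**4. Gain in the log binomial model.** This uses the large-sample (sandwich) variance of the treatment effect, with maternal history only versus maternal, paternal and sibling history. BMI is left out, which amounts to giving it no effect.

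| RR for each relative | SE, maternal only | SE, all three | Power | Variance change | Equivalent women (of 586) |
|---|---|---|---|---|---|
| 1.0 | 0.1470 | 0.1470 | 78.8% → 78.8% | 0 | 0 |
| 1.2 | 0.1470 | 0.1466 | 78.8% → 79.0% | −0.5% | 3 |
| 1.5 | 0.1467 | 0.1445 | 78.9% → 80.1% | −3.0% | 18 |
| 2.0 | 0.1462 | 0.1367 | 79.2% → 84.3% | −12.5% | 84 |

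The last column is 586 × [1/(1 − reduction) − 1]; for 3.0% this is 586 × (1/0.970 − 1) ≈ 18.

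**5. Simulation of the same eligible population.** There were 1,000 trials per scenario, with BMI in the model. Mean SE, stratification variables only versus added covariates:

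- RR 1.0: 0.1480 vs 0.1479
- RR 1.2: 0.1480 vs 0.1475
- RR 1.5: 0.1478 vs 0.1454
- RR 2.0: 0.1473 vs 0.1379 (trials where both models fitted)

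With no treatment effect and RR 1.5 for each relative, both models rejected in 5.2% of trials. An ordinary log binomial fit of the larger model failed in 0 of 1,000 trials at RR 1.2, 2 at RR 1.5 and 137 at RR 2. The smaller model never failed.

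**6. Poisson regression with robust variance.** In a simulation of eligible families the power gains were about 0.4, 0.9 and 2.7 points at RR 1.2, 1.5 and 2. There was no penalty when there was no association, and no inflation of type I error. The gain at RR 2 is smaller than the 84.3 − 79.2 ≈ 5 points in step 4 because this estimator makes less use of the differences in risk between cells.

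**The case against.** The strongest reply is that nothing here is wrong. Adjusting for the stratification variables matches the randomisation and produces no bias, no alpha error and no contradiction, and the sample size stands without any covariate gain. The document is also a condensed article. It does not say that only the stratification variables will be used, and an analysis plan that is not shown may name more. All of this stands, so the point is an optional efficiency gain and depends on what that plan says.

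A reader might infer that the contrast between 30% here and up to one in five in infants generally shows family history to be a strong predictor within the trial. It does not. That contrast sets at-risk infants against infants generally, and every enrolled infant already has an affected first-degree relative. The documents give no association between paternal or sibling history and eczema among such infants, nor do they call family history the main driver of eczema.

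A reader might also infer that precision is being given away at no cost. That is too strong. The gain is zero if there is no association and small if the association is weak. Fit failures are most frequent where the gain is largest. Sibling history needs a coding rule for infants without siblings, as does any unknown paternal history.

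What survives is narrower: the data are scheduled for collection at baseline, the candidates follow from the trial's own definition of risk, and the calculations show no loss in mean SE when they turn out to be uninformative.

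**Conclusion.** The point holds as a small, low-cost improvement to a valid primary analysis. Adding paternal and sibling history would raise power by about 0.2 to 0.4 points if each relative's history has a relative risk of 1.2, about 1 point at 1.5, and about 3 to 5 points at 2.0. The lower end at 2.0 is for robust Poisson regression and the upper end for the log binomial model. With no association the gain is nil.

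These sizes rest on assumed prevalences and prognostic strengths, 293 evaluable infants per group, and the planning rates of 30% and 20%. The estimated quantity is unchanged by the extra covariates only if the relative risk for treatment is constant across family-history groups. The documents do not support reading this as bias, as an error in the plan, or as a certain loss of precision.

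**What to change.** Unless the analysis plan already names these covariates, add the following to it before unblinding (section 2.4 keeps the blind until all 12-month assessments are complete):

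- Primary model: allocated group, maternal allergy status, maternal BMI group, paternal allergy history (yes/no/unknown) and sibling allergy history (yes/no, with no sibling coded as no).
- Fallback if the log binomial model does not converge: a named method that also targets the relative risk, such as Poisson regression with robust variance.
- Supporting analysis: the model with the stratification variables only.

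The cost is a few sentences and no new data. The downside is two more covariates, the coding rules, and more frequent log binomial non-convergence if the predictors prove strong, which is why the fallback has to be fixed at the same time.

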### 2.8. Monitoring Adherence to Study Powder Ingestion

During the intervention period the research team maintain regular (in-person or telephone) monthly contact with participants to monitor and encourage study powder consumption adherence, as well as to answer any questions as they arise. If the participant stops taking the study powder, she is asked to provide a reason for ceasing study powder ingestion. The participating women return their unused powder tins for weighing at the end of the intervention period when their infant is six months of age.

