### 2.9. Trial Outcomes

The primary outcome for this trial is infant medically diagnosed eczema by 1 year of age. 

The secondary clinical outcomes (all participants) are: Infant medically diagnosed IgE-mediated food allergies by 1 year of age.Infant medically diagnosed recurrent wheeze by 1 year of age.Infant allergic sensitisation to food and environmental allergens at 1 year of age.Maternal and infant skin barrier permeability at 36 weeks (maternal only), 3–4 and 6 months post-natal, and at 1 year of age (infant only).Maternal weight gain during the pregnancy and lactation intervention period, gestational length, and pregnancy complications (including gestational diabetes mellitus, pre-eclampsia and gestational hypertension).Infant birth anthropometrics and body composition.Infant weight gain and growth during infancy.The secondary laboratory outcomes are:Maternal immune responses at 20, 28 and 36 weeks of gestation.Maternal gut microflora colonisation patterns and stool short-chain fatty acid levels and composition during the pregnancy and lactation intervention period.Infant gut microflora colonisation patterns and stool short-chain fatty acid profiles at 2, 3–4, 6 and 12 months of age.Infant immune responses at birth, 3–4, 6 and 12 months of age.Breast milk composition and immune components at 2, 3–4, 6 and 12 months of age.

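### The six-month per-protocol set is selected on powder intake that early eczema or side effects can influence; the antenatal set removes only the eczema-driven part

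*Protocol article*

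**What the plan says.** Section 2.16 makes intention to treat the basis of analysis: "Analyses will be performed on an intention-to-treat basis (i.e., all randomised women analysed as randomised". It then plans two further analyses of the primary outcome. Both are labelled sensitivity analyses and neither is ranked above the other.

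- **Six-month set:** "A sensitivity per-protocol analysis of the primary outcome will be undertaken in women that consumed at least 75% of their allocated study powder", judged from returned tins and measured "during the entire intervention period (<21 weeks gestation to 6 months post-natal".
- **Antenatal set:** women who took the powder "on at least 75% of the days between randomisation and 36 weeks of gestation (last clinic visit prior to birth".

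The only adjustment the section names is for the stratification variables, which section 2.4 gives as maternal allergy status and pre-pregnancy BMI.

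On the outcome, section 2.9 states: "The primary outcome for this trial is infant medically diagnosed eczema by 1 year of age". Section 2.12 places visits at 3–4 and 6 months, where "The infant is examined for clinical signs of allergic disease (ie eczema), and SCORAD [43] (severity and extent of eczema) assessments performed if relevant". It also has telephone calls at 1, 2 and 5 months that record infant allergy symptoms. Each month of the intervention "the participating women are asked about their compliance with the study powder ingestion, any adverse gastrointestinal symptoms, stool frequency and consistency". Section 2.8 adds: "If the participant stops taking the study powder, she is asked to provide a reason for ceasing study powder ingestion". No analytic use of those reasons is stated.

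**The concern.** Membership of the six-month set is fixed by behaviour up to six months after birth, while the outcome accumulates from birth to one year. For about half of the outcome period, exposure is still being classified while events occur. A mother whose infant develops eczema at two months counts as an event, and she may also stop the powder and so leave the set because of that event.

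The monthly questions on gastrointestinal symptoms point to a second route. If tolerability differs between prebiotic and maltodextrin, and tolerance or persistence is related to the infant's eczema risk, the adherent women in the two arms are no longer alike. This route is open for both sets.

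At stake is how the per-protocol results are read. A sensitivity analysis is usually taken as a test of whether the main result is robust. Here the comparison gives up the protection of randomisation, so a per-protocol relative risk that differs from the intention-to-treat one could reflect selection and not the effect of taking the powder.

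**Working it through.** **Plan's own figure (section 2.15).** With 30% versus 20%, two-sided 5%, 80% power and pooled variance: n = [1.96·√(2·0.25·0.75) + 0.842·√(0.3·0.7 + 0.2·0.8)]² / 0.10² ≈ 293.2. This is the stated 293 (294 if rounded up). 293/0.9 = 325.6, so 326 per group and 652 in total. The planning figures are sound and serve as inputs below.

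**Inputs not in the article (assumed).** Adherence rates; share of eczema diagnosed by six months (f = 0.4–0.8); relative drop in adherence after early eczema (d = 0.2–0.4); adherence pattern by risk; benefit from partial intake.

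**1. Can early eczema move a woman out of the set?** Take birth at 40 weeks and six months as 26 weeks. With entry at 20 weeks the window is 20 + 26 = 46 weeks, and 75% of it is 34.5 weeks. A fully adherent woman fails if she stops before 34.5 − 20 = 14.5 weeks after birth. With entry at 18 weeks the window is 48 weeks, 75% is 36, and the limit is 36 − 22 = 14 weeks. So eczema in about the first three months can exclude a fully adherent woman. Later eczema excludes only women who had already missed doses.

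**2. Outcome-driven stopping, six-month set.** If early cases have adherence a(1 − d) and all others a, the risk in the set is r = p(1 − fd)/(1 − pfd); a cancels. No true effect, p = 0.30:

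| f·d | r in the affected arm | RR, drop in prebiotic arm only | RR, drop in placebo arm only |
|---|---|---|---|
| 0.4·0.2 = 0.08 | 0.276/0.976 = 0.283 | 0.94 | 1.06 |
| 0.8·0.2 or 0.4·0.4 = 0.16 | 0.252/0.952 = 0.265 | 0.88 | 1.13 |
| 0.8·0.4 = 0.32 | 0.204/0.904 = 0.226 | 0.75 | 1.33 |

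If the drop is the same in both arms, the RR stays 1.00. With a true RR of 0.667 and equal drops, it becomes 0.661 (f·d = 0.08) to 0.644 (f·d = 0.32).

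**3. Side-effect selection, either set.** Let half the women be at lower and half at higher risk, with placebo adherence 75% in both halves. In the prebiotic arm adherence is 75% in the lower-risk half and 50% or 35% in the higher-risk half. No true effect, so the placebo set stays at 0.30.

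- Risks 25/35%, adherence 75/50%: (0.75·0.25 + 0.50·0.35)/1.25 = 0.290, RR 0.97.
- Risks 20/40%, adherence 75/35%: (0.75·0.20 + 0.35·0.40)/1.10 = 0.264, RR 0.88.

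The direction follows from the assumption. With the 50% adherence in the lower-risk half, the first case gives (0.50·0.25 + 0.75·0.35)/1.25 = 0.310, RR 1.03.

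**4. Size against sampling error.** With 293 evaluable women per arm, the RR of 0.88 in step 3 compares about 220 placebo women (75%) with 161 prebiotic women (55%). SE(log RR) = √(0.7/0.3/220 + 0.736/0.264/161) ≈ 0.167, so the shift is 0.129/0.167 ≈ 0.8 SE. For the most extreme case in step 2 (205 versus about 185 women, RR 0.75), SE ≈ 0.173 and the shift is 0.285/0.173 ≈ 1.65 SE.

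**5. Complier-average estimate.** Risk difference = intention-to-treat difference / adherent share in the prebiotic arm. At the planned −0.10 and 70% adherence it is −0.10/0.70 = −0.143; at 50% it is −0.200 and at 90% it is −0.111. It is zero when the intention-to-treat difference is zero. If women below 75% get a fraction g of the full benefit, it is inflated by 1 + g(1 − π)/π, where π is the adherent share. With g = 0.5 this is 1.50, 1.33, 1.21 and 1.12 at π = 50, 60, 70 and 80%.

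**The case against.** The strongest reply is that this is a conventional secondary analysis, openly labelled, behind an intention-to-treat primary analysis. The same section already supplies an antenatal version that eczema cannot influence. Setting the two results side by side gives a reader some view of whether postnatal selection matters. The trial is double-blind, so stopping because of eczema has no obvious reason to differ by arm, and step 2 then gives no bias under no effect and very little otherwise. The article reports no difference in tolerability. Further causal estimators may be in an analysis plan that is not shown.

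Most of this stands, and it rules out three stronger readings that a reader might infer.

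- **That the main analysis is compromised.** It is not. Both analyses are sensitivity analyses, and no conclusion is stated to depend on them.
- **That the per-protocol result will show a false benefit.** The documents do not support this. The bias can go either way, material size needs arm-differential stopping that is not shown, and in the side-effect scenarios the shift is below one standard error.
- **That a complier-average estimate removes the difficulty.** It keeps the randomised comparison but replaces one assumption with another. Women below 75% still take some powder, and women who stop later have already been exposed. Because it rescales the intention-to-treat difference, it also adds little evidence on whether any effect exists.

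What the reply does not remove is that the stated rule for the six-month set uses intake after the outcome can begin, and that the antenatal set remains open to selection by side effects and prognosis. The point rests on rules the article states, not on what it leaves out.

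**Conclusion.** The point holds as a modest improvement to the secondary analyses. The six-month set conditions on behaviour that early eczema or side effects can drive. The 36-week set removes the first influence and keeps the second. The intention-to-treat result is untouched.

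Under no effect the bias is zero when stopping follows the same pattern in both arms. It is about 0.88–0.97 on the relative risk in the side-effect scenarios, and about 0.75–1.33 for the six-month set if only one arm stops after early eczema. The ends of the last range need 80% of eczema to be diagnosed by six months and a 40% relative drop in adherence in one arm alone. By step 1, only fairly early eczema can exclude a fully adherent woman, so those ends are unlikely. All these figures are illustrations, because the article gives no adherence rates, no timing of eczema and no arm difference in stopping.

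**What to change.** In section 2.16, or in the analysis plan before unblinding:

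1. Keep the six-month subset comparison as descriptive, and say that entry to it can depend on the outcome and on side effects. Tabulate adherence and the recorded reasons for stopping by arm.
2. Give the antenatal adherence measure priority among the adherence-based analyses.
3. Add a supplementary complier-average risk difference on the full randomised set: randomisation as instrument, the antenatal 75% definition, adjustment for the stratification variables and a bootstrap confidence interval. Report it beside the intention-to-treat relative risk, not in place of it.
4. State the exclusion restriction and that it is only approximate, because women below 75% receive part of the powder and may continue it after birth. Add a sensitivity analysis that allows partial benefit (as in step 5) or treats dose as continuous.

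The cost is some extra analysis of data already collected. The downsides to state are a confidence interval wider by roughly 1/adherence, a risk-difference scale where the primary result is a relative risk, and an antenatal measure counted in days and not from tin weights, since tins are returned for weighing only at six months.
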